#### The effectiveness of NSEIT/NSE

Background data will be collected, including age, sex, symptom duration, and whiplash injury or other reason for neck pain.

The primary outcome measure that will be collected is neck-specific function as measured by the Neck Disability Index (NDI) [42].

The secondary outcome measurements will be pain intensity (current, average last week, worst pain last week) in the neck, head, and arm, and dizziness (current, average last week, worst dizziness last week) in the past week, using a numeric rating scale (NRS, score 0 to 10: 0 = no pain or dizziness, 10 = worst imaginable pain or dizziness) [43]; answers to questions about health-related quality of life; work ability measured with the Work Ability Score (WAS) reporting “current work ability compared to highest work ability ever” (score 0 to 10; 0 = cannot work at all, 10 = best work ability [44]; and patient’s improvement or deterioration over time, measured with an 11-point global rating scale (GRS: − 5 = vastly worse, 0 = unchanged, 5 = completely recovered) [45]. Any adverse events or negative effects will be registered at the 3-month follow-up.

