### Statistical analyses

All analyses will be conducted in collaboration with a statistician. Data will be analyzed according to intention to treat and supplemented with per protocol analysis. An analysis will be done of the missing data. Imputation methods may be used when deemed to have additional value. Subgroup analyses of age, gender, neck pain intensity, headache, and dizziness may possibly be performed.*Data regarding the implementation strategy* will be analyzed using a parametric t-test and a linear mixed model or repeated-measures ANOVA or the non-parametric Mann-Whitney U test and Kruskal-Wallis test, depending on the data. Analyses will evaluate differences between groups A and B and changes in variables over time.*Data regarding the effectiveness of NSEIT and NSE* will be analyzed with a linear mixed model or repeated-measures ANOVA or Kruskal-Wallis, depending on the data. NDI, pain intensity, headache, and dizziness will be evaluated as dependent variables with time as an independent fixed factor (baseline, 3 months, and 12 months after start of intervention). The results will be compared with the results from the RCT studies [8, 12].

The effect of neck-specific exercises in the present study for WAD grades II and III and for patients with other neck-pain disorders will also be evaluated and compared with the results in the RCT studies [8, 12].

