### Sample size

Sample size and power regarding group differences were calculated by a statistician. The aim of the study is to evaluate both implementation and effectiveness. The sample size calculation to evaluate implementation was based on the assumption that 15% more patients will receive neck-specific exercises in the intervention group (40% in the intervention group and 25% in the control group). The required sample size under individual randomization will be 150 patients in each arm. With 10 physiotherapy clinics (clusters) in each arm (a total of 20 clusters), intra-cluster correlation of 0.02 and a cluster size of 21 patients, a total of 420 patients will be recruited for 80% power and a significance level of 0.05. To ensure that enough people are in each group after dropouts, a total of 500 patients will be included, 25 patients from each cluster.

Sample size calculation to evaluate effectiveness was based on a clinically relevant improvement of 7% in the NDI, an effect size of 0.2 (Cohen’s f) or 0.4 (Cohen’s d), a correlation among repeated measures of 0.3, and the need for a total of 56 participants for 80% power and a significance level of 0.05. With an expected dropout rate of 20%, a total of 70 participating patients will be needed. The total number of patients may be more than 70 because patients will be recruited at each clinic.

Repeated-measure ANOVA or a linear mixed model will be used to examine changes in the patient-reported outcomes over time (i.e., at baseline and 3 and 12 months). The results will be compared with the results from the RCT studies [8, 12]. Patients who are included in both the intervention and control implementation groups and receive neck-specific exercises will be treated as one group in terms of the effect of the intervention. Analyses will be performed with parametric statistics if assumptions of normality are met, and otherwise with non-parametric statistics.

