### Limitations

The limitations of the present study are related to the pragmatic approach. To study the implementation process and the adoption, diffusion, and maintenance of the NSEIT/NSE in clinical practice we could not follow as strict a protocol as in an RCT, which means we have less control over the study. The physiotherapists will select patients whose condition they have deemed to be improved by neck-specific exercises. Because all patients will be evaluated as one group, with no comparison with other treatments or exercise methods, threats to internal validity exist; that is, threats to confidence that the results are trustworthy. However, we will compare the results with the findings in our previous RCTs. Threats to the study’s external validity arise from the fact that only neck-pain patients and physiotherapy clinics that are interested in participating in the study will be evaluated. With these concerns in mind, the results can be generalized to physiotherapy clinics in primary care, as many different regions and physiotherapy clinics will participate in the study.

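### Kruskal-Wallis, an independent-samples test, is the only non-parametric option named for one group of patients measured at baseline, 3 and 12 months

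*Protocol article*

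**What the plan says.** Under Statistical analyses, the protocol article states that data on the effectiveness of NSEIT and NSE "will be analyzed with a linear mixed model or repeated-measures ANOVA or Kruskal-Wallis, depending on the data". It then enters NDI, pain intensity, headache and dizziness as dependent variables "with time as an independent fixed factor (baseline, 3 months, and 12 months after start of intervention". NDI is the primary effectiveness outcome.

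Under Sample size, the two implementation arms are merged for this purpose: "Patients who are included in both the intervention and control implementation groups and receive neck-specific exercises will be treated as one group". The Limitations section confirms that there is no comparator: "Because all patients will be evaluated as one group, with no comparison with other treatments or exercise methods".

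The rule for leaving the parametric methods also stands under Sample size: "Analyses will be performed with parametric statistics if assumptions of normality are met, and otherwise with non-parametric statistics". Kruskal-Wallis is the only non-parametric test named for the effectiveness data. No rank test for repeated measures, such as Friedman or Wilcoxon signed-rank, appears anywhere in the article.

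**The concern.** With one pooled group and time as the factor, the levels compared are three measurements on each patient. Kruskal-Wallis treats them as three unrelated samples. It judges the differences between time points against the full spread of scores, including the stable differences between patients, which cancel out of a within-patient comparison. The reference distribution is therefore wrong, and increasingly so as the correlation between visits rises.

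The fallback could plausibly be used. Pain and dizziness are rated from 0 to 10, and such bounded scores can be skewed; NDI falls under the same normality rule. At stake is the validity of the p-value for change over time in NDI and, depending on the correlation and the number analysed, some of the power the sample size was meant to secure.

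**Working it through.** **Inputs from the Sample size section.** Effect size: "an effect size of 0.2 (Cohen’s f) or 0.4 (Cohen’s d"). Correlation among repeated measures 0.3; N = 56 for 80% power at the 0.05 level; 70 after 20% dropout. Three time points (m = 3).

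**Step 1: the plan's own figure.** For a within-patient F test with sphericity, the noncentrality is λ = f² × N × m / (1 − ρ) = 0.04 × 56 × 3 / 0.7 = 9.6, with 2 and (56 − 1) × 2 = 110 degrees of freedom. Power is 78.7%, and 80% is reached at N = 58. Dropout: 56 / 0.8 = 70. The stated figures are reproduced within 2 patients. They match only a three-visit analysis that uses the correlation of 0.3, so the sample size relies on the pairing that Kruskal-Wallis discards.

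**Step 2: true size of Kruskal-Wallis, by hand.** With equal correlation between visits and no true change, the statistic behaves in large samples roughly as (1 − ρ) times a chi-square with 2 degrees of freedom, where ρ is strictly the correlation between ranks. The upper tail of that chi-square at x is exp(−x/2), so the true size is about 0.05^(1/(1 − ρ)).
- ρ = 0.3: 0.05^(1/0.7) = 0.014.
- ρ = 0.5 (assumed; not in the article): 0.05² = 0.0025. This is slightly low, because the rank correlation is a little below 0.5.

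**Step 3: simulation.** Normal scores, equal variances, equal correlation between visits, no clinic clustering, N = 56, nominal level 5%. Power is at f = 0.2. The ranges cover repeated simulations of 6,000 or 20,000 runs, with means following a linear trend or an early change that is then sustained.

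| ρ | Kruskal-Wallis size | Friedman size | Kruskal-Wallis power | Friedman power |
|---|---|---|---|---|
| 0.3 (plan) | 1.3–1.5% | 5.2% | 59–60% | 64–65% |
| 0.5 (assumed) | 0.3–0.4% | 4.9–5.3% | 59% | 79–80% |

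Kruskal-Wallis power hardly moves with the correlation, because the test makes no use of it. The gap to a paired test therefore widens as the correlation rises.

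**Step 4: larger sets at ρ = 0.3.** Kruskal-Wallis against Friedman: about 72% and 74% at N = 70, 79% and 80% at N = 80, and 89% and 89% at N = 100.

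**Step 5: one skewed shape.** With lognormal scores (sigma 0.6, pure location shift, latent correlation 0.3, f = 0.2, N = 56, 3,000 runs), both rank tests had about 93% power. This is a single illustrative shape, assumed here, and other shapes would give other figures.

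**The case against.** Kruskal-Wallis is the third of three options. The linear mixed model and repeated-measures ANOVA named before it suit paired data. The Sample size section names only those two for change over time, and its normality sentence says non-parametric statistics without naming a test. All of this stands: the faulty test is reached only if normality is judged to fail and the list under Statistical analyses is then followed as written. It limits the severity but does not correct the wording.

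One might also say that Kruskal-Wallis is meant for comparing diagnosis groups. The text does not fit that reading: the sentence that follows makes time the factor, and the comparison across WAD and other neck pain comes in a separate paragraph.

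A reader might infer that the fallback costs about 20 points of power, from 79% for repeated-measures ANOVA to 59%. That contrast comes from normal data, for which the plan's rule keeps the parametric analysis. Once the rule has sent the data to rank methods, the fair comparator is a paired rank test, and at the plan's correlation the difference is about 5 points.

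A reader might also object that repeated-measures ANOVA would confine the analysis to completers. The article does not fix that: it plans intention to treat, an analysis of missing data and possible imputation, and it has already raised 56 to 70 for dropout.

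**Conclusion.** The point holds as an error in the named test. An independent-samples test is specified for repeated measurements on one group, and nothing elsewhere in the article corrects it. If it is used, the nominal 5% test runs at about 1.4% at the plan's correlation of 0.3, and at about 0.4% if the correlation is assumed to be 0.5.

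The direction is conservative. It would be wrong to infer that the fallback could produce a false claim of effectiveness: under positive correlation between visits it rejects too rarely. The power cost against Friedman at N = 56 and f = 0.2 on normal scores is about 5 points at 0.3 and about 20 points at an assumed 0.5. It can be negligible for skewed scores at 0.3 or when more patients are analysed, and the article expects that the number may exceed 70.

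These sizes rest on equal variances, equal correlation between visits and no clinic clustering, none of which the article states. The mismatch between test and design does not depend on them. Severity: should be fixed. The faulty test is a conditional fallback, and the methods listed ahead of it are suitable.

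**What to change.** In the effectiveness paragraph of Statistical analyses, replace Kruskal-Wallis for time effects with a method for repeated measures. Either of two choices is sufficient:
- a paired rank test: Friedman across the three visits, with Wilcoxon signed-rank for pairwise contrasts; or
- the linear mixed model already named, with robust or bootstrap intervals when residuals are not normal.

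Keep Kruskal-Wallis only for comparisons between independent groups. Let the normality sentence under Sample size refer to the chosen method, so that the two sections agree. The implementation paragraph also lists Kruskal-Wallis and covers change over time as well as group differences, so the same restriction belongs there.

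Friedman restores the 5% level at any correlation but recovers only part of the power when the correlation is low and scores are normal; the mixed model avoids that loss. The cost is a change of wording, with no effect on data collection, patient numbers or conduct.

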#### Secondary outcome

The Evidence-Based Practice Attitude Scale (EBPAS) will be used to assess the physiotherapists’ attitudes to implementation of evidence-based practice [39] and will be collected only at baseline. The questionnaire includes 15 items, each answered on a 5-point scale from 0 (not at all) to 4 (agree completely). The total score ranges from 0 to 60, and higher scores indicate more favorable attitudes. The questionnaire can be divided into four different scales: scale 1 (requirements), scale 2 (appeal), scale 3 (openness), and scale 4 (divergence). Self-efficacy and confidence in diagnosing and treating patients with neck pain will be measured by use of the Practitioner Confidence Scale (PCS) [40]. The PCS will be collected before and directly after the theoretical and practical education, and at the 3- and 12-month follow-ups. A total of 4 items are reported by the practitioner and a total score is collected, where 4 represents greatest self-confidence and 20 represents lowest self-confidence.

The secondary outcome measures will also include questions about each physiotherapist’s experience of the neck-specific program: the number of times the physiotherapist had contact with the patient (visits, telephone, and/or chat) and information about additional or other exercises and/or treatment for neck pain will be collected via the medical record and/or the web-based support and treatment platform INERA, and/or through the Swedish Classification of Health Interventions [41].

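### Kruskal-Wallis, a test for independent samples, is the only rank-based fallback named for change over time in the same patients; its p-value is invalid there and should be removed from those analyses

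*Protocol article*

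**What the plan says.** In the protocol article, under Statistical analyses, the patient-level effectiveness data "will be analyzed with a linear mixed model or repeated-measures ANOVA or Kruskal-Wallis, depending on the data". The next sentence takes NDI, pain intensity, headache and dizziness as the dependent variables, "with time as an independent fixed factor (baseline, 3 months, and 12 months after start of intervention".

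The Sample size section adds two things. Patients from both implementation arms who receive the exercises "will be treated as one group in terms of the effect of the intervention", so no between-arm factor is left in this analysis. The switch to the fallback is then stated: "Analyses will be performed with parametric statistics if assumptions of normality are met, and otherwise with non-parametric statistics". The same section says that repeated-measures ANOVA or a mixed model will be used for patient-reported change over time, and it bases the effectiveness sample size on "an effect size of 0.2 (Cohen’s f) or 0.4 (Cohen’s d") with a correlation among repeated measures of 0.3.

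For the implementation data, the listed methods are a t-test, a mixed model, repeated-measures ANOVA, or "the non-parametric Mann-Whitney U test and Kruskal-Wallis test, depending on the data". The purpose covers both contrasts: "Analyses will evaluate differences between groups A and B and changes in variables over time". One of the implementation outcomes is the practitioner confidence score: "The PCS will be collected before and directly after the theoretical and practical education, and at the 3- and 12-month follow-ups".

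The article names no rank test for paired or repeated measurements.

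**The concern.** Kruskal-Wallis compares three or more independent samples. Here there is one group of patients, measured three times. If the normality condition fails, the text leads to Kruskal-Wallis across the three occasions, and two things go wrong.

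First, the reference distribution is wrong. With positive within-person correlation the occasion means vary less against each other than independent samples would. The nominal 5% test rejects too rarely, and the pairing that the sample size relies on is thrown away.

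Second, patients are no longer compared with themselves. All patients at baseline are set against whoever remains at 3 and 12 months, so a change in who is present can pass for a change in score.

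NDI is the primary outcome of the effectiveness evaluation, so the choice matters if the fallback is used. The point concerns pairing within a person; clustering by clinic is a separate matter.

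**Working it through.** **Inputs.** From the Sample size section: f = 0.2, d = 0.4, correlation ρ = 0.3, n = 56, 80% power, significance level 0.05, 20% dropout. From Statistical analyses: m = 3 occasions. Assumed here: the 7% improvement is 7 NDI points, so SD = 7/0.4 = 17.5; equal correlation between all occasions. All other correlations, distributions and dropout patterns below are also assumptions.

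**The plan's own figure.** For one group and a within-person factor, λ = n·m·f²/(1−ρ) = 56 × 3 × 0.04/0.7 = 9.6, with 2 and 110 degrees of freedom. Power is 78.7%; 58 patients give 80.2%. The stated 56 is reproduced to within two patients, and 56/0.8 = 70 is exact. The sample size is therefore a within-person calculation, with ρ in the denominator.

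**Type I error of Kruskal-Wallis over time.** With three occasions the statistic is referred to chi-square on 2 degrees of freedom. With common correlation ρ it behaves approximately as (1−ρ) times that variable, so the true level is about 0.05^(1/(1−ρ)):
- ρ = 0.3: 0.05^(1/0.7) = 1.4%. Simulation at n = 56 gives 1.3 to 1.8%, on normal and on skewed data.
- ρ = 0.5: 0.05² = 0.25%. Simulation gives 0.3 to 0.4%.

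At ρ = 0.3, repeated-measures ANOVA (4.7 to 5.3%) and Friedman's test (5.2 to 5.5%) keep their level on normal data.

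**Power, normal data, n = 56, ρ = 0.3.** A 7-point fall held at 3 and 12 months, means (0, −7, −7), has f = 7 × (√2/3)/17.5 = 0.189. Then λ = 56 × 3 × 0.0356/0.7 = 8.5 and repeated-measures ANOVA has 73% power. Simulated power of Kruskal-Wallis is about 52% (51 to 55% across runs). At the plan's f = 0.2 it is 60% against 79%.

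**Power, skewed data.** Normal data would not trigger the fallback, so the comparison was repeated with skewed scores of the same SD. Kruskal-Wallis reached about 95%, Friedman about 95% and repeated-measures ANOVA about 71%. The power loss did not appear there.

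**Dropout, nobody changing.** Assume 20% leave, leavers score 10 points worse throughout, and ρ = 0.3. The baseline mean of everyone exceeds that of the remainers by 0.2 × 10 = 2 points, which reads as improvement. Kruskal-Wallis rejects in about 4% of samples at n = 56, 4 to 5% at n = 70, 8 to 10% at n = 160 and 33% at n = 500. If the leavers are better than average, the sign reverses.

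**Does pairing cure this?** Only for some dropout mechanisms. In the scenario above, complete-case paired tests stay near 5%, because a constant shift cancels within each person. If instead the chance of leaving rises with the baseline score (about 20% lost, ρ = 0.3), rejection with no true change is:

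| Test | n = 70 | n = 500 |
|---|---|---|
| Kruskal-Wallis | 2–3% | 6–7% |
| Friedman, complete cases | 9–10% | 39–43% |
| Wilcoxon signed-rank, complete cases | 12% | 52% |

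A linear mixed model on all available data kept the estimated 12-month change within 0.02 SD of zero, checked at n = 500.

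**The case against.** The strongest reply is that this is a fallback. The mixed model and repeated-measures ANOVA are listed first, the Sample size section says that one of these will be used for patient-reported change, its fallback sentence names no test, and a statistician is involved. That stands as a reason to grade the point below a critical fault. It does not remove it: the same paragraph lets a normality check override the parametric methods, and Statistical analyses names Kruskal-Wallis as the only rank-based replacement, directly before naming time as the factor.

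A second reply is that the test errs on the safe side. Without dropout this is true: the p-value is too large, and no false claim of benefit follows from ignoring the correlation. The cost is power, and that cost is shown only on normal data.

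Third, a reader might infer that the plan will report improvement where there is none. The documents do not support that at the planned size: rejection is about 5% at 70 patients even in the unfavourable scenario, and no direction or strength of dropout is given. Inflation becomes possible only in much larger samples, which the plan allows, since 500 patients are to be recruited and it says that the effectiveness sample may exceed 70.

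Fourth, a reader might infer that Kruskal-Wallis is expressly assigned to the repeated confidence scores. It is not: the implementation paragraph gives one pooled list of tests for group differences and for change over time. With two arms, Mann-Whitney already covers the group contrast, so time is the likely use, but that is inference.

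**Conclusion.** The point holds as a should-fix. As written, failure of normality leads to a test for independent samples on three repeated measurements of the same patients. At the plan's correlation of 0.3 and n = 56 its true type I error is about 1.5% instead of 5%. On normal data it gives up about 20 percentage points of power for a sustained 7-point fall; under skewness the loss depends on the distribution and may be absent. These figures assume an SD of 17.5 and equal correlation across occasions.

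The dropout consequence is conditional. It needs selective dropout and a sample well above 70, and it can look like improvement or deterioration depending on who leaves. The 33% rejection at n = 500 belongs to one assumed scenario. Nor may one conclude that any paired rank test would be safe: when dropout depends on the baseline score, the complete-case paired tests did worse than Kruskal-Wallis. For the confidence scores the conclusion is only that Kruskal-Wallis should not be used for their change over time, since the pooled list permits it.

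**What to change.** Delete Kruskal-Wallis from every analysis of change over time, for patients and for physiotherapists. Name the linear mixed model with a patient (or physiotherapist) random effect, fitted to all available data, as the single analysis, in place of a choice that depends on a normality check. If residuals are clearly non-normal, keep that framework and use a transformation, an ordinal link or a bootstrap.

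Friedman's test, or Wilcoxon signed-rank from baseline to 3 and to 12 months, may be added as sensitivity analyses only. State with them that they use complete cases and are biased when dropout depends on the baseline score. Mann-Whitney can stay as a rank-based comparison of the two arms at a single occasion, as far as this point goes.

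The cost is one or two sentences in Statistical analyses and a matching edit to the last sentence of Sample size. No patients, visits or data are added.

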### Participants and settings

Twenty physiotherapy clinics in primary health care in Sweden will be included. Twenty-five patients with neck pain will be consecutively recruited from each clinic, for a total of 500 patients. The flow diagram can be seen in Fig. 1 and the planned schedule of enrollment, interventions, and assessments in Fig. 2.

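### The pooled NDI analysis names no clinic term and permits methods that cannot carry one, so its error bars will be too narrow if clinics differ in NDI change

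*Protocol article*

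**What the plan says.** Under Statistical analyses, the effectiveness data "will be analyzed with a linear mixed model or repeated-measures ANOVA or Kruskal-Wallis, depending on the data", and "NDI, pain intensity, headache, and dizziness will be evaluated as dependent variables with time as an independent fixed factor", the time points being baseline, 3 and 12 months. The Sample size section repeats the choice between repeated-measures ANOVA and a linear mixed model, and makes parametric or non-parametric analysis depend on normality. Patients from both implementation arms who receive the exercises "will be treated as one group in terms of the effect of the intervention". No clinic or physiotherapist term is mentioned for these outcomes.

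The effectiveness sample size rests on Cohen's f of 0.2, "a correlation among repeated measures of 0.3, and the need for a total of 56 participants for 80% power and a significance level of 0.05". Allowing for dropout, "With an expected dropout rate of 20%, a total of 70 participating patients will be needed". The paragraph before it, on the implementation outcome, uses 20 clusters, an ICC of 0.02 and a cluster size of 21. Participants and settings states: "Twenty-five patients with neck pain will be consecutively recruited from each clinic, for a total of 500 patients".

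**The concern.** The same clinics are clusters for one primary outcome and do not appear in the analysis or sample size of the other. The stated rule for choosing a method looks at the data and at normality, and clustering plays no part in it. A patient-level repeated-measures ANOVA would therefore follow the plan as written. Its error term is patient-by-time variation and contains no separate clinic-by-time component.

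Variation in change between clinics is plausible under this design. Physiotherapists progress the exercises individually and book visits as they see fit. They may deliver the internet or the supervised version and may add other treatment. Only the ten clinics in group A get workshops and chat support, and the two arms are then merged.

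What is at stake is the precision of the NDI change. The effectiveness question asks whether the results match those of the earlier RCTs, and the Limitations section confirms that there is no concurrent comparator. Understated error could make ordinary clinic-to-clinic variation look like a difference from the RCTs.

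**Working it through.** **1. The plan's own figures.** For a one-group repeated-measures ANOVA with 3 time points, the noncentrality is λ = f² × N × 3 / (1 − ρ). With f = 0.2, N = 56 and ρ = 0.3, λ = 0.04 × 56 × 3 / 0.7 = 9.6. On 2 and 110 df at alpha 0.05 this gives 78.7% power, and N = 58 reaches 80%. So 56 is reproduced to within 2 patients without any clustering term, and 56 / 0.8 = 70. By contrast, the implementation calculation uses 1 + (21 − 1) × 0.02 = 1.40, and 150 × 1.40 × 2 = 420 as stated. The design effect is in one calculation and absent from the other.

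**2. Which clinic variation matters.** The target is change within patients, so a clinic difference in NDI level cancels. A clinic random intercept alone would therefore not help. The relevant quantity is the ICC of NDI change, meaning the share of the variance of change that lies between clinics. The document does not give it. The value 0.02 is borrowed from the implementation outcome as an assumption, with a range of 0 to 0.05.

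**3. Analysed patients per clinic (m).** The effectiveness group is limited to patients who receive the exercises. On the plan's 40% and 25%, the average is 32.5% of 25, or about 8 per clinic. The recruitment section, however, enrols patients judged suitable for the exercises, so up to 25 is possible. Both values are shown.

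**4. Size of the effect.** Design effect DE = 1 + (m − 1) × ICC. The correct interval is √DE times wider. Coverage of a nominal 95% interval that ignores clinic is P(|Z| < 1.96/√DE).

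| m | ICC | DE | √DE | 1.96/√DE | Coverage |
|---|---|---|---|---|---|
| any | 0 | 1.00 | 1.00 | 1.96 | 95% |
| 8 | 0.02 | 1.14 | 1.07 | 1.84 | about 93% |
| 25 | 0.01 | 1.24 | 1.11 | 1.76 | about 92% |
| 25 | 0.02 | 1.48 | 1.22 | 1.61 | about 89% |
| 25 | 0.05 | 2.20 | 1.48 | 1.32 | about 81% |

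A simulation of the unadjusted interval with 20 clinics of 25 gave 94.8%, 92.4%, 89.9% and 81.1% coverage at ICC 0, 0.01, 0.02 and 0.05.

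**5. False-positive rate of the 3-time ANOVA.** Simulation used 4,000 runs per setting, ρ = 0.3, no true change, and clinic-by-time variance set to the ICC share of within-patient variance. With 25 per clinic the rate was 5.5% at ICC 0, 13.5% at 0.02 and 25.5% at 0.05. With 8 per clinic it was 7.1% at 0.02 and 10.6% at 0.05. A check by formula: with 2 numerator df and many denominator df, P(F > c) is close to exp(−c). The critical value is about 3.0, so ICC 0.02 gives exp(−3.0/1.48), about 13%, for 25 per clinic and exp(−3.0/1.14), about 7%, for 8. An ANOVA on clinic means held 4.6% to 5.6% throughout.

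**6. Power at the stated size.** With 56 patients over 20 clinics, m = 2.8 and DE = 1 + 1.8 × 0.02 = 1.036. Power falls from 78.7% to 77.1%, or to 74.9% at ICC 0.05. Even if patients came 25 to a clinic, the need at ICC 0.02 would be 56 × 1.48, about 83. About 160 analysed patients (8 × 20) would exceed that.

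**The case against.** The strongest reply is that a linear mixed model is the first method listed and could carry clinic. The sentence on time concerns the fixed factor only and excludes no random effect, and random-effects structure is commonly settled in an analysis plan that is not shown here. This stands in part. A reader might infer that patients are certain to be treated as independent; the article does not say so. It does, however, leave two methods open that cannot account for clinic, under a selection rule unrelated to clustering.

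Secondly, a reader might infer that the NDI interval is too narrow, full stop. The documents do not support that either. Clinic differences in level cancel, no ICC for change is given, and 0.02 belongs to a different, binary outcome. The standardised education and the shared set of exercises may hold clinic variation down. The point must stay conditional.

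Thirdly, 25 per clinic is the least favourable case. On the plan's own percentages the number is nearer 8, where the effect is modest.

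Fourthly, the plan states no interval, test or margin for the RCT comparison, and the 7% NDI improvement is only a sample-size input. The Limitations section already admits that the one-group design and therapist-selected patients threaten internal validity. All this is fair. It limits how much weight the comparison can bear, but it does not justify an error term that leaves clinic out.

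Lastly, the missing design effect might be read as an underpowered effectiveness study. The power figures above do not bear that out.

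**Conclusion.** The point holds in conditional form. For the NDI, the plan names no clinic term and permits patient-level methods that cannot carry one, although it allows for clustering in the same clinics elsewhere. If clinics differ in NDI change, those methods give error bars that are too narrow.

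At an assumed ICC of 0.02 for change, the understatement runs from slight (8 analysed patients per clinic) to material (25 per clinic). It vanishes at ICC 0 and is serious at 0.05 with 25 per clinic. The size rests on that borrowed ICC and on the number analysed per clinic, neither of which the article fixes. A finding of some overall improvement may well survive; the precision of the comparison with the RCTs is more exposed. The sample size needs no change. The plan should be amended, since a better method can be named now at almost no cost.

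**What to change.** For the NDI and the other patient-reported outcomes, replace patient-level repeated-measures ANOVA and Kruskal-Wallis as the basis for inference with one of the following:

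- a linear mixed model with time as a fixed factor, a patient random effect and a clinic-by-time random effect; or
- mean changes at 3 and 12 months with clinic-level cluster-robust standard errors and a small-sample t reference (20 clinics, about 19 df).

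Use the resulting interval in the comparison with the RCTs. State the ICC assumed for NDI change. Add a note to the Sample size section that 56 (70 with dropout) assumes no between-clinic variation in NDI change.

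The change is one of wording. Patients are recruited clinic by clinic, so clinic is known for each of them, and no extra recruitment is needed. The price is a somewhat wider interval: about 1.07 times at 8 per clinic and 1.22 times at 25, if the ICC of change is 0.02.
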